### Participant timeline {13}

Enrollment, randomization, and the intervention (or usual care) will occur on day 0. Follow-ups will occur at approximately 14 days and 60–75 days, allowing for multiple attempts at contact up to 16 weeks. Follow-up can occur by text, email, or phone, per patient preference (Table 1).

**Table 1 Tab1:** Time schedule of data collection and study procedures

Procedure	Screening/enrollment (day 0)	Follow-up 1 (day 14)	Follow-up 2 (day 60–75)
Informed consent	X		
Demographics	X		
Medical History	X		
Randomization	X		
Intervention	X		
Patient knowledge test	X		
Patient engagement survey	X		
Trust in Physician Scale	X		
SDM measures	X		
Clinical outcomes (ED diagnosis, HRDwC, ED revisits, 30/60 day CT usage, admission rate, urologic procedures, primary care visits)	X	X	X
Patient Satisfaction survey	X		
Clinicians’ perspectives assessment	X		

*HRDwC* High risk diagnosis with complications

### Sample size {14}

As per Fig. 3, three discrete analysis times are planned.

Our sample size for phase I (until interim analysis 1) is based on the expert recommendation that at least 50 subjects be included to examine the pragmatics of recruitment [30].

For the endpoint of reduction in the use of CT scans, assuming a base proportion of 80% (currently, the usage rate for kidney stones), a sample of 200 patients (100 patients per group) will provide 87% power to detect a reduction of CT use to 60%, as significant at a *p* value of 0.047 (adjusted to account for the interim efficacy analysis—see explanation below). A final sample size of 200 is large enough to account for a loss of 10% and still provides about 80% power to detect the hypothesized difference. If lost to follow-up rates are higher, a sample size of 250 will be used (125 patients per group).

For the endpoint of knowledge, we hypothesize that an improvement of 2 points (of 10) is clinically significant. If the decision aid improves knowledge from 6/10 to 8/10, we will be powered at 0.80 to detect this with a total of 70 participants.

### Recruitment {15}

Currently, internal data suggests that > 300 patients per year meet inclusion criteria at our primary site, and research staff will be available to approach approximately 1/3 of those who meet criteria. If recruitment is slower than expected, we will expand the length of the trial or enroll participants at one of our 5 community sites. We may also be able to alter research staffing to increase availability of staff during off hours (nights and weekends).

## Assignment of interventions: allocation

### Sequence generation {16a}

#### Randomization

Patients will then be randomized via permuted blocked randomization [31, 32]. Randomization will be stratified by “history of stones” with separate randomization for subjects with a history of kidney stones, as the decision aid for these patients is different, because guidelines suggest avoiding CT for young healthy patients with a history of kidney stones [33]. Allocation will be based on a 1:1 ratio between the intervention and usual care arms. Though we will not be able to blind clinicians to use of the decision aid, patients will not be aware of whether they are receiving usual care or the decision aid, as the consenting information will refer to paper-based information—which accurately describes both the decision aid and the usual care information packet. The research staff will maintain a database recording randomization, which will be separate from general subject-level data and will not be accessible to the PI or statisticians until planned interim analyses.

### Concealment mechanism {16b}

Groups of 4–10 pre-composed opaque envelops will be ordered via subject number and kept in a locked research office, and the envelopes will be distributed sequentially.

### Implementation {16c}

The PI and Research Coordinator will generate pre-composed opaque envelopes to be used for randomization. Trained research staff will enroll patients and assign participants to interventions based on the order of the envelops.

## Assignment of interventions: blinding

### Who will be blinded {17a}

Participants will be blinded to the specific purpose of the trial and to their allocated group; therefore, all patient-centered outcomes (e.g., knowledge) will be gathered from patients who are blinded to group allocation. The consent will inform them that they were being randomized to one of two “ways to receive information,” without specific mention of the role of the decision aid in decision-making. Clinicians and study staff will not be blinded. Feasibility analysis (recruitment and retention) will be blinded, but fidelity analysis (for fidelity to intervention and contamination) will require analysts to know the treatment group of each participant.

### Procedure for unblinding if needed {17b}

As clinicians and study staff are not blinded, unblinding will not occur.

## Data collection and management

### Plans for assessment and collection of outcomes {18a}

Research coordinators will screen all patients seeking care at the study site who have a chief complaint of “flank pain” or “possible kidney stone.” Data from screened patients will be entered into a secure RedCap online standardized data collection form. (All study data will be collected and managed using *REDCap* electronic data capture tools hosted at Tufts University.)

In addition, working clinicians will be prompted via emails, training, and signs in the ED to contact study staff if they have a patient they deem possibly eligible. Reasons for exclusions will be documented, including reasons the patient was not approached or self-reported reasons they did not consent.

Research staff will confirm and document eligibility prior to informed consent. After written informed consent, they will collect baseline variables such as demographics, characteristics of chief complaint, and results of available ED testing. The research staff will note the study assignment in a separate RedCap database, so that the remainder of the study materials are blinded (e.g., the RA assessing the follow-up will not know the intervention group).

After the intervention or usual care is delivered, research staff will collect outcome data on patient knowledge, satisfaction, trust in physician, and the decision made. Standardized data collection forms will be used or data will be entered directly into the RedCap database. Audio recordings will be made of the conversation, if both patient and clinician consent and a conversation occur. These recordings will be independently rated with the OPTION-5 score by two trained team members who are blind to the intervention group [25].

Participants will be given a healthcare diary and follow-up procedures will be explained (Supplementary Material 5). Participants will be contacted 2 weeks and 8 weeks after their visit via phone, email, or text. A standardized follow-up script will assess safety and healthcare utilization. Events occurring within 8 weeks will be recorded and confirmed via chart review. Participants will be asked to sign an authorization so that records for care taking place outside the hospital system can be obtained. Utilization and safety data will include patient-reported data but will be confirmed with chart review and will include subsequent ED visits, CT scans, admissions, procedures, and diagnoses.

Clinicians will be surveyed after each encounter with a brief paper-based survey. If time allows, several open-ended questions will be asked and the answers will be audio recorded. The questions will assess the clinician’s perception of patient involvement in decision-making, the helpfulness of the information, and the efficiency of the interaction.

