### Who will take informed consent? {26a}

A study coordinator will identify potentially eligible patients based on the chief complaint and, in collaboration with the treating clinician, confirm patient eligibility for the trial (Fig. 2). The study coordinator will then obtain written informed consent from the patient. Verbal consent will be obtained from participating clinicians at the time of patient consent—if clinicians agree to be recorded. Patients will be consecutively enrolled five to seven days per week whenever a study coordinator is available for enrollment.

Consent for audio recordings will be separate from the consent for the trial and lack of consent for recording will not preclude participation in the trial. Clinicians will verbally consent to recording as well—if either the patient or the clinician does not consent, the conversation will not be recorded. If no conversation takes place regarding diagnostic options, a recording will not be made.

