#### Integrating patient recruitment, consent, and delivery of the intervention in the flow of patient care

Figure 2 shows how the process of patient recruitment, consent, randomization, and delivery of the intervention will integrate with the flow of patient care. We will assess patient eligibility and obtain consent shortly after the clinician has evaluated the patient, treated their pain, and begun diagnostic testing (but prior to ordering a CT scan). Patients will then be randomized and receive the intervention or usual care. Patients for whom an exclusion criterion becomes apparent post-randomization (ex. patient who develops a fever, has a positive pregnancy test, or is found to have a solitary kidney on ultrasound) will be classified as screen failures and not analyzed [24].

Patients who are randomized to the decision aid arm will then be given the decision aid, and the clinician will be prompted to discuss the diagnostic options. For the purposes of blinding, patients randomized to usual care will receive a paper informational sheet and the clinician will be prompted to proceed with usual care regarding diagnostic imaging.

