##### Certainty (“risk”) assessment and delivery of the intervention

The study coordinator will collect pre-intervention variables from patients, including the components of the STONE score [8]. The coordinator will collect and collate relevant variables from the clinician, including ultrasound results. The clinician will receive a document clarifying the patient’s STONE score and the meaning of that score (Ex. Moderate STONE score + mild hydronephrosis = 90% chance of stone) (see Supplementary Material 2). The study coordinator will then provide the clinician with a color copy of the decision aid to provide a concise refresher of the content. There are two areas of the decision aid where the clinician will be prompted to enter data personalized to the patient. First, they will be prompted to fill in a line about pre-test probability, based on the STONE Score and the ultrasound results. Second, they will be given the option of indicating their recommendation prior to the conversation. The decision aid will then be given to the patient, and the study coordinator will give the patient at least 15 min to read the decision aid prior to discussion with the clinician. The treating clinician will then, using the KSC decision aid as a tool to facilitate a conversation, educate the patient regarding the rationale for their clinical suspicion up to that point in the ED visit and engage the patient in a shared decision regarding whether to obtain a CT at that time.

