##### Usual care

Participants in the usual care group will receive an informational intervention. This two-page pamphlet contains relevant information about kidney stones developed as part of the decision aid development process, but does not address decision-making or the use of CT scans. Clinicians who have a patient in the usual care group will be encouraged to continue care as usual. Stakeholder engagement has suggested usual care may include the use of CT, ultrasound, and/or shared decision-making. The usual care group will not have access to the decision aid.

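### Eligibility is to be confirmed before consent, yet randomisation can precede the pregnancy test or ultrasound result for some patients, and only the aid-arm procedure then seeks the ultrasound

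*Protocol article*

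**What the plan says.** Two sections of the protocol article put confirmation of eligibility before consent. Outcome collection {18a} states: "Research staff will confirm and document eligibility prior to informed consent". The consent section {26a} has the coordinator, "in collaboration with the treating clinician, confirm patient eligibility for the trial (Fig. 2"), and only then obtain consent.

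The section on integrating recruitment and consent into patient care sets the eligibility check and consent at a point when the clinician has seen the patient, "treated their pain, and begun diagnostic testing (but prior to ordering a CT scan"). The next step is: "Patients will then be randomized and receive the intervention or usual care". No step waits for results. The section then names patients in whom an exclusion emerges after randomisation: one who develops a fever, "has a positive pregnancy test, or is found to have a solitary kidney on ultrasound". They "will be classified as screen failures and not analyzed". Sections {11b} and {20a} repeat the removal.

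The arms differ in what happens to the ultrasound. Under the intervention-arm description {11a}, the coordinator gathers ultrasound results from the clinician. Clinicians also complete part of the aid before the patient receives it: "they will be prompted to fill in a line about pre-test probability, based on the STONE Score and the ultrasound results". For the comparator the article says: "Clinicians who have a patient in the usual care group will be encouraged to continue care as usual". It notes that usual care may include ultrasound, but no step there asks for a result. Section {17a} states that clinicians and study staff are not blinded.

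**The concern.** A new fever is a later event and does not conflict with an earlier eligibility check. Pregnancy and a solitary kidney are different: both are already true when the patient consents. If the plan expects them to surface first after allocation, eligibility was not fully confirmed before consent in those patients.

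The timing matters because it creates post-randomisation exclusions, and one kind of them may depend on arm. Once the envelope is open, an unblinded clinician with an aid-arm patient has a reason to obtain or chase an outstanding ultrasound that a usual-care clinician does not have. Disqualifying findings on ultrasound could then be detected, and the patients removed, at different rates in the two arms. The analysed groups would no longer be exactly those that randomisation formed. Ultrasound findings first obtained after allocation also could not be treated as baseline characteristics, should anyone wish to adjust for them.

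**Working it through.** **The order of events.**

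| Step | {18a} and {26a} | Integration section |
|---|---|---|
| Eligibility | Confirmed before consent | Checked when testing has begun |
| Consent | After confirmation | At the same stage |
| Randomisation | Order relative to results not stated | Next, with no wait for results |
| Pregnancy, solitary kidney | Should already be known | May appear after randomisation |

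The two columns agree only if confirmation means confirmation on what is known so far. The text does not say so.

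**The plan's own power figure.** Inputs from {14} and {21b}: CT use 80% against 60%, 100 per arm, two-sided 0.047 (z = 1.986).

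- Standard error under the null: √(0.7 × 0.3 × 2/100) = 0.0648.
- Standard error under the alternative: √((0.16 + 0.24)/100) = 0.0632.
- Power: Φ[(0.20 − 1.986 × 0.0648)/0.0632] = 87.0%.

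The stated 87% reproduces and is not in question.

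**Excess exclusions in the aid arm.** The documents give no rates. Assumptions: a share q = 3% to 5% of patients has an exclusion that ultrasound would reveal, and ultrasound is done in 95% of the aid arm and 60% to 80% of usual care. The excess is q × (difference in ultrasound use):

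- low: 0.03 × (0.95 − 0.80) = 0.0045, about 0.5 per 100;
- high: 0.05 × (0.95 − 0.60) = 0.0175, about 1.8 per 100.

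The pregnancy test is not tied to one arm. If the 3% to 5% includes pregnancies, these figures are upper bounds.

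**Effect on the CT comparison, high case.** Removed: f = 0.05 × 0.95 = 4.75% of the aid arm and g = 0.05 × 0.60 = 3% of usual care. Take no true effect, 80% CT in both arms, and let c be the CT rate among those removed. The analysed rates are (0.80 − f·c)/(1 − f) and (0.80 − g·c)/(1 − g).

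| c | Aid arm | Usual care | Spurious difference (aid minus usual care) |
|---|---|---|---|
| 0% | 0.80/0.9525 = 84.0% | 0.80/0.97 = 82.5% | +1.5 points |
| 80% | 80.0% | 80.0% | 0 |
| 100% | 0.7525/0.9525 = 79.0% | 0.77/0.97 = 79.4% | −0.4 points |

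**Outer bound.** Suppose removal occurs only in the aid arm, with 100 randomised per arm and nominal error 0.047:

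| Removed from aid arm | c = 100%: spurious reduction; type I error | c = 0%: spurious increase; type I error |
|---|---|---|
| 2% | 0.4 points; 0.048 | 1.6 points; 0.056 |
| 5% | 1.1 points; 0.051 | 4.2 points; 0.113 |

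Equal removal in both arms gives no bias and leaves the error at 0.047.

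**The case against.** The best defence is that the sections can coexist. The eligibility check covers what is known at consent, and a separate rule handles criteria that emerge later, as is common in emergency department trials. Testing that has begun may be complete for many patients, and {18a} collects available test results from everyone. Fig. 2, which holds the flow and the exclusion list, is not shown and might fix the order. Much of this stands: the results are outstanding for some patients, not necessarily all. But the article's own text expects facts that already exist at consent to appear after allocation, so the wording still needs reconciling.

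The arm difference is also softer than it may look. Section {11a} prompts the clinician to use ultrasound results but orders no ultrasound, and usual care may include one. What remains is that only one arm has a step that seeks the result, in the hands of unblinded staff.

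A reader might infer that a lower CT rate in the aid arm would reflect added ultrasound rather than the decision aid. The documents do not support calling that confounding. {8} describes a pragmatic trial of a risk-stratified aid that may act through its effects on providers, and {11a} builds the ultrasound-based probability into it. Ultrasound prompted by the aid can fairly be read as part of the intervention. Nor can a gap in ultrasound use be set beside the 20-point CT effect, because they are different quantities.

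Loss of ultrasound as a covariate is hypothetical, since the analysis sections do not name it.

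**Conclusion.** The concern holds in a limited form. The article places confirmation of eligibility before consent, yet lets some patients be randomised with a deciding pregnancy test or ultrasound outstanding, and then removes those found ineligible. Because the ultrasound result is sought only in the aid-arm procedure, its exclusions could be found somewhat more often there.

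The likely size is small: about 0.5 to 1.8 excess exclusions per 100, and in the high case a spurious CT difference between a 0.4-point reduction and a 1.5-point increase. This rests wholly on assumed rates. The direction depends on the CT rate among those removed, and the bias vanishes if that equals the overall rate. The stated power is unaffected. The change is worth making because it costs little and removes most of the problem at its source.

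**What to change.** Reconcile {26a}, the integration section and {18a}. Keep consent where it is. Open the envelope only once the pregnancy test (where applicable) and any ultrasound already planned before the CT decision have resulted, and the exclusion criteria have been re-checked and documented. Mandate no ultrasound. Record whether an ultrasound was done before randomisation as a baseline variable, and report by arm both ultrasound use and exclusions after randomisation.

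The cost is protocol wording, slightly later randomisation, and a few consented patients who are never randomised. The delay should be short, because only an ultrasound that the CT decision already awaits is waited for. Staff must still randomise before a CT is ordered. Ultrasounds first requested after allocation could still differ by arm, which is why they should be reported.

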#### Outcome measures: efficacy

We selected outcome measures via input from the Steering Committee, patients, and practicing clinicians as well as previous literature [26]. We also have included in the post-enrollment survey a measure assessing outcome priorities in the studied population. As stakeholders generally represent two different groups (patients and clinicians), we considered two outcomes as primary [27]. Clinicians endorsed radiation exposure as the most important primary outcome, measured as the proportion of patients receiving a CT scan during the ED visit and within 60 days and total radiation exposure in 60 days. Patients endorsed knowledge as a primary outcome, and the steering committee created and piloted a 10 question knowledge test.

We also selected a number of secondary outcomes based on stakeholder input. Secondary efficacy outcomes include 1 - clinician effort to engage patients in SDM (OPTION-5 scale), 2 - patient engagement as measured by CollaboRATE and SDM question(s), 3 - patient satisfaction (items from the Hospital Consumer Assessment of Healthcare Providers and Systems [HCAHPS]), 4 - trust in physician (trust in physician scale, 5 questions) and several implementation outcomes regarding the helpfulness of the intervention (see post-encounter patient and clinician data collection forms, Supplementary Materials 3 and 4) [25, 28, 29].

Safety outcomes include the primary outcome of radiation exposure (number of CT scans obtained on day 0 and within 60 days), total radiation in 30 days/60 days (milli-gray [mGy]) from diagnostic imaging, and the incidence of high-risk diagnoses with complications (HRDwC) that could be related to missed or delayed diagnoses. These HRDwC have been previously defined [10].

Operational outcomes will include (1) ED revisits (in 7/30/60 days) and hospital admissions on second visit, (2) ED length of stay (LOS) (minutes), (3) admission rate, (4) final diagnosis for initial visit, (5) 60-day alternative diagnoses, and (6) urologic procedures (in 30/60 days).

Implementation outcomes will include (1) clinicians’ ratings of conversation/decision aid (“would you recommend,” “would you use again,” and qualitative feedback), (2) acceptability (clinicians’ ratings, qualitative and quantitative), and (3) Fidelity (RA checkboxes) as well as adherence to protocol.

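### The data-collection section records events only to 8 weeks (day 56), while CT use, radiation and other outcomes are defined to day 60; the two windows must be reconciled

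*Protocol article*

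**What the plan says.** Three parts of the Protocol article bear on how long events are counted.

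- **Outcome measures: efficacy.** The radiation outcome, one of two primary outcomes, is "measured as the proportion of patients receiving a CT scan during the ED visit and within 60 days and total radiation exposure in 60 days". The safety outcomes repeat it as the "number of CT scans obtained on day 0 and within 60 days". ED revisits, alternative diagnoses and urologic procedures also have 60-day versions.
- **Participant timeline {13} and Table 1.** "Follow-ups will occur at approximately 14 days and 60–75 days, allowing for multiple attempts at contact up to 16 weeks". Table 1 marks the clinical outcomes row, which names CT usage at 30 and 60 days, for collection at that second follow-up.
- **Plans for assessment and collection of outcomes {18a}.** "Participants will be contacted 2 weeks and 8 weeks after their visit via phone, email, or text". Then, on what is kept: "Events occurring within 8 weeks will be recorded and confirmed via chart review".

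No section says which of these takes precedence.

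**The concern.** Section 18a makes two separate statements with an 8-week limit. One is about when to call. The other is about which events are recorded and checked against the chart. Both stop short of the 60 days over which the outcomes are defined, and the call date also falls before the second follow-up scheduled in Table 1.

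The recording limit matters more. The timeline says when to make contact; section 18a says what to write down. A CT on day 58 lies inside the outcome definition but outside the recording rule, even if the participant is reached on day 65. A later call does not by itself settle the conflict.

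At stake is whether a primary outcome is ascertained over the same period in everyone. If some staff work from section 18a and others from the timeline, one participant's count may end at day 56 and another's at day 60, under the same outcome label.

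**Working it through.** **Inputs**

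| Item | Value | Source |
|---|---|---|
| Second contact | 8 weeks | Section 18a |
| Events recorded and chart-confirmed | within 8 weeks | Section 18a |
| Second follow-up | day 60–75 | Section 13, Table 1 |
| Limit for contact attempts | 16 weeks | Section 13 |
| CT, radiation, revisits, alternative diagnoses, procedures | to 60 days | Outcome measures: efficacy |
| Assumed CT use, size, test level | 80% v 60%, 100 per group, two-sided 0.047 | Sample size {14}, Interim analyses {21b} |

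**The plan's own figure.** The only computed figure in this area is the 87% power for CT use. With pooled variance under the null and no continuity correction:

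- Null standard error: √(2 × 0.70 × 0.30 / 100) = 0.0648.
- Alternative standard error: √((0.80 × 0.20 + 0.60 × 0.40) / 100) = 0.0632.
- Power: Φ[(0.20 − 1.986 × 0.0648) / 0.0632] = 87.0%.

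The stated 87% reproduces. The follow-up window does not enter this calculation, so correcting it changes neither power nor sample size.

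**The windows**

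- Section 18a: 8 × 7 = day 56.
- Shortfall against the outcome definition: 60 − 56 = 4 days (days 57–60).
- Share of the calendar window: 4 / 60 = 6.7%.
- Distance from the earliest day of the second follow-up: 60 − 56 = 4 days.
- Limit for contact attempts: 16 × 7 = day 112.

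**Side by side**

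| Rule followed | Days of the 60-day window not recorded |
|---|---|
| Section 18a, literally | 4 (days 57–60) |
| Section 13 and Table 1, with events counted to day 60 | 0 |
| Contact per section 13, recording limit per section 18a | 4, although contact comes after day 60 |

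The last row shows why the recording sentence, and not only the call date, has to change.

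**What is untouched.** CT during the ED visit and the knowledge test are measured on day 0. The 7- and 30-day outcomes end well before day 56.

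**The case against.** The strongest reply is that the formal schedule already covers the full window. The timeline and Table 1 place the second follow-up at day 60–75 and collect 60-day CT usage there. Section 18a may only be speaking loosely: it writes 2 weeks where the timeline writes approximately 14 days, so 8 weeks may stand for about 60 days. This reading is plausible, but the text does not confirm it. It also fits the call date better than the recording limit, which is a rule about which events count. The objection lowers the seriousness of the point but does not remove the contradiction.

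Four stronger readings are tempting, and the document does not support them.

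- **That 60-day outcomes cannot be complete.** They can be, if staff follow the timeline and Table 1 and count events to day 60.
- **That the outcome window could stretch to week 16.** Sixteen weeks limits attempts at contact. The outcome definition stays at 60 days, and events are confirmed by chart review, so a late call does not lengthen the window.
- **That the omission favours the decision-aid arm.** The argument would be that late scans matter most in patients not scanned on day 0, and that these are 40% v 20% by arm. The sample size section does not say that its 80% and 60% are day-0 rates. For total radiation, repeat scans count in either arm, and the background section says that many patients have two or more CTs per episode.
- **That 6.7% of events would be lost.** The figure is a share of days. The background section says that most stones pass within several weeks, so the last four days probably hold few events.

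**Conclusion.** The point holds as an internal contradiction with a small probable effect. The contact and recording rules in section 18a end 4 days before the 60-day outcomes do, and they conflict with the day 60–75 follow-up. Depending on which section staff follow, CT use and radiation to 60 days, together with the 60-day revisits, alternative diagnoses and procedures, may be incomplete or ascertained over unequal windows.

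The 4-day figure assumes that 8 weeks means 56 days; if the authors meant about 60 days, only the wording is wrong. The document gives no event rate for days 57–60, so the number of missed events and any difference between arms cannot be calculated. That the loss is small is a judgement from the expected early timing of events, not a computed result. The point deserves correction because it touches the definition of a primary outcome and is nearly free to repair.

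**What to change.** In section 18a, change two sentences.

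1. **Contact.** Replace the 8-week contact with the window already in the timeline: second follow-up at day 60–75, no earlier than day 60, with attempts continuing to 16 weeks.
2. **Recording.** Replace the 8-week limit with a statement that events dated day 0 to day 60 are recorded and confirmed by chart review for every participant in both arms, whenever contact succeeds. Events after day 60 learned of at a late contact are not counted in the 60-day outcomes.

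The cost is a two-sentence correction and a call schedule that never places the second contact before day 60. The sample size, power and test levels do not change. Recruitment has been open since December 2019, so if any participants were followed only to day 56, their records should be checked through day 60 by the same procedure in both arms.
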